### Sample size

According to a previous study (32), the mean itch intensity was taken as 35.7% for the EA group, 40.4% for the sham electroacupuncture (SEA) group, and 45.9% for the sham acupuncture (SAC) group, with *α* = 0.05, test efficacy 1-β = 0.8, two-sided test, using the estimation of sample size formula for comparing more than two treatment groups [referring to 
$n=2{\left(\sigma \frac{Z_{1-\alpha /\left(2\tau \right)}+Z_{1-\beta }}{\mu_{A}-\mu_{B}}\right)}^{2}$
, 
$1-\beta =\Phi \left(Z-Z_{1-\alpha /\left(2\tau \right)}\right)+\Phi \left(-Z-Z_{1-\alpha /\left(2\tau \right)}\right)$
, 
$Z=\frac{\mu_{A}-\mu_{B}}{\sigma \sqrt{\frac{2}{n}}}$
, where Φ is the standard normal cumulative distribution function, 
$\mu_{A}\;\mathrm{and}\;\mu_{B}$
 representing the mean of any two groups, and n is the sample size of a pair of τ comparisons (taking the maximum value)]. Consequently, the sample content was calculated to be 35 cases per group and 105 cases for the three groups. Assuming a 20% dropout rate of patients at follow-up, we calculated the sample size to be 44 cases for each group and 132 participants for the three groups (EA, SEA, and SAC). Participants will be recruited from two research centers, each targeting 66 participants.

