### Outcome measures

#### Primary outcome measure

The proposed study’s primary outcome is improved VAS scores after 2 weeks of treatment. VAS scores are designed to be measured at the screening phase, after 1 week of treatment, and after 2 weeks of treatment. Pruritus, the main clinical symptom of eczema, can be scored separately on the VAS (35).

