### Statistical analysis

Professional statisticians developed a statistical analysis plan upon consultation with the primary investigators. The data will be stored in the Data Management Center of Jiangsu Famous Medical Technology Co. Ltd. and processed by in-house statisticians blinded to group allocation.

All statistical analyses are performed using R [version 4.1.3; R Core Team (2022). R: A language and environment for statistical computing. R Foundation for Statistical Computing, Vienna, Austria^2^]. Statistical significance is set at value of *p* < 0.05. The intention-to-treat analysis population, consisting of all participants who pass the randomization stage, will be the primary population for demographic and other baseline characteristics, compliance, efficacy analysis, and safety analysis.

The analytical methods will be combined with descriptive and comparative analyses. Qualitative data will be described by frequency tables, percentages, or composition ratios; comparative analyses will be conducted using the chi-squared test, Fisher’s exact test, Wilcoxon rank-sum test, Cochran–Mantel–Haenszel test, and weighted least-squares covariance. Quantitative data will be described as the mean, standard deviation, median, quartile, minimum, and maximum. The *t*-test will be used for comparative analysis of data with normal distributions and with Satterthwaite correction if the variance is uneven. Quantitative data exhibiting a non-normal distribution on the Wilcoxon rank-sum test will be analyzed using the Wilcoxon signed-rank sum test and covariance generalized linear models. A sensitivity analysis for the primary outcome with the most conservative data (the worst or best outcome of that indicator in the group) will assess the robustness of the missing data at random assumption. A multiple imputation will be used to impute missing values.

The hypothesis test is two-sided; the test statistics and their corresponding *p*-values will be reported.

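### If the primary VAS is judged normal, the only stated test is a t-test without baseline adjustment; one prespecified ANCOVA would be at least as precise at no extra cost

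*Protocol article*

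**What the plan says.** The Statistical analysis section of the protocol article assigns methods by type of data, not by endpoint. For quantitative data judged normal, the t-test "will be used for comparative analysis of data with normal distributions and with Satterthwaite correction if the variance is uneven", and no covariate is mentioned. Quantitative data judged non-normal "will be analyzed using the Wilcoxon signed-rank sum test and covariance generalized linear models", again with no covariates named. The list for qualitative data ends with "Cochran–Mantel–Haenszel test, and weighted least-squares covariance". Covariance methods thus appear for two kinds of data and not for the third, normal quantitative data.

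Under Primary outcome measure: "The proposed study’s primary outcome is improved VAS scores after 2 weeks of treatment". This does not settle whether the analysed quantity is the week-2 score or the change from baseline. The same section says "VAS scores are designed to be measured at the screening phase, after 1 week of treatment, and after 2 weeks of treatment", so a baseline value is planned for every participant. No sentence ties a particular test to the VAS.

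Two other sections bear on the point. Randomization and allocation describes permuted blocks without stratification. Eligibility criteria limits body surface area but sets no minimum itch score.

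**The concern.** The VAS is quantitative. If it is judged normal, the general rule sends it to a two-group t-test, and the screening VAS is then either unused or merely subtracted. Neither is the best use of it. A week-2 comparison ignores what baseline predicts; a change score over-corrects whenever the baseline–outcome correlation is below 1 and the variances are equal.

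The design does nothing to balance baseline itch, because randomisation is not stratified and entry does not restrict the score. Adjustment in the analysis is the remaining protection. Whether a covariance model is used at all would depend on a distributional check on the outcome, and the check named in the article, a Wilcoxon rank-sum test, does not test normality.

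At stake are the width of the confidence intervals for EA against each sham arm, and how far each estimate moves with a chance difference at baseline. The Discussion itself names the sample size as a limitation.

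**Working it through.** **Step 1: the plan's own figures.** The dropout step reproduces: 35 / 0.8 = 43.75, so 44 per group, and 3 × 44 = 132. The 35 per group cannot be reproduced, because the Sample size section states neither σ nor the number of comparisons τ. For EA and SEA it gives these means: "the mean itch intensity was taken as 35.7% for the EA group, 40.4% for the sham electroacupuncture (SEA) group". The third mean, in the SAC arm, is 45.9. The differences are 4.7, 5.5 and 10.2. The smallest, 40.4 − 35.7 = 4.7, governs the maximum n. Solving the article's formula backwards, with two-sided α = 0.05 and power 0.80:

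σ = 4.7 × √(35/2) / (z(1−α/(2τ)) + z(0.80))

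- τ = 3: 4.7 × 4.183 / (2.394 + 0.842) = 6.08
- τ = 2: 6.38
- τ = 1: 7.02

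These values only calibrate what follows: they give a t-test on the week-2 score 80% power at 35 per arm. They are not figures from the article.

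**Step 2: variances.** Assume equal variance σ² at baseline and week 2, and correlation ρ between them. The article gives no ρ, so a range is shown. The outcome variance entering the comparison is:

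- t-test on week-2 score: σ²
- t-test on change: 2σ²(1 − ρ)
- ANCOVA: σ²(1 − ρ²)

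ANCOVA relative to the week-2 t-test is therefore 1 − ρ². Relative to the change t-test it is (1 − ρ²) / (2(1 − ρ)) = (1 + ρ)/2. Neither ratio exceeds 1 for ρ between 0 and 1. The price is one degree of freedom.

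| ρ (assumed) | ANCOVA / week-2 t-test | ANCOVA / change t-test |
|---|---|---|
| 0.3 | 1 − 0.09 = 0.91 | 1.3/2 = 0.65 |
| 0.5 | 1 − 0.25 = 0.75 | 1.5/2 = 0.75 |
| 0.7 | 1 − 0.49 = 0.51 | 1.7/2 = 0.85 |

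**Step 3: what this means for power.** With τ = 3 and 35 per arm, power ≈ Φ(3.236/√V − 2.394), where V is 1, 2(1 − ρ) or 1 − ρ².

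| ρ (assumed) | week-2 t-test | change t-test | ANCOVA | n per arm for 80% with ANCOVA |
|---|---|---|---|---|
| 0.3 | 80% | 63.3% | 84.1% | 32 |
| 0.5 | 80% | 80.0% | 91.0% | 27 |
| 0.7 | 80% | 96.3% | 98.4% | 18 |

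With τ = 1 the ANCOVA powers are 83.6%, 89.9% and 97.5%, so the unstated τ hardly matters here. The variance ratios in step 2 do not depend on n, so they hold equally for 44 randomised per arm.

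**Step 4: chance imbalance.** Suppose two arms differ by chance by 1 VAS point at baseline. Under the same assumptions, the week-2 comparison is shifted on average by ρ points: 0.3, 0.5 or 0.7. The change comparison is shifted the other way by 1 − ρ: 0.7, 0.5 or 0.3. ANCOVA removes the linear part of this shift.

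**The case against.** The strongest reply is that the article does not fix an unadjusted primary analysis. A reader might infer that it does, but the t-test reaches the VAS only through the general rule and only if the data are judged normal. A bounded itch score in patients with limited skin involvement may well be skewed, and the plan then names a covariance model. That stands, and the point is limited accordingly.

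Second, the article says that a statistical analysis plan was developed, and it is not shown. Covariates are commonly left to such a plan, and it may specify the adjustment. This does not dispose of the point. The article states a method for normal data and places covariance methods elsewhere, which is a choice of method, not a detail left out.

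Third, the unadjusted test agrees with the sample-size formula, which compares two means with no baseline term. It does, and the test is valid; that does not make it the better choice.

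Fourth, if improvement means change from baseline, the t-test already uses the baseline in part. This also stands. The remaining problem is then over-correction, and the loss against ANCOVA is greatest at low correlation.

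Fifth, the gain is uncertain. Against a week-2 t-test at ρ = 0.3 it is about 4 power points.

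A further argument, that pairwise t-tests waste the third arm's variance information, carries no weight. Pooling raises the degrees of freedom from 68 (2 × 35 − 2) to 102 (3 × 35 − 3), which moves the critical t from about 2.00 to 1.98, and it assumes equal variances.

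**Conclusion.** The point holds in limited form. For normal quantitative outcomes, which would include the primary VAS if it is so judged, the article names only a t-test with no baseline covariate, although the baseline VAS is to be collected. ANCOVA would reduce the variance by 9% to 51% against a week-2 t-test and by 15% to 35% against a change t-test, over assumed correlations from 0.3 to 0.7 and with equal variances at the two times.

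Three stronger readings are not supported:

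- **Bias.** A reader might infer that the planned comparison is biased. Under randomisation it is not; the loss is in precision and in protection once a chance imbalance has occurred.
- **Strong prediction.** A reader might infer from the missing itch threshold that baseline VAS varies widely and predicts the outcome strongly. The article gives neither a baseline standard deviation nor a correlation.
- **Only 35 analysed per arm.** That is the planning figure after dropout. The primary population is everyone randomised, 44 per arm, with multiple imputation.

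This is an efficiency gain worth taking before the data are unblinded, not an error that invalidates the analysis.

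**What to change.** State the primary analysis as one prespecified ANCOVA: week-2 VAS on arm (three levels) and baseline VAS, in all randomised participants, with the planned multiple imputation for missing values. Make it apply whatever a normality check shows. Report the adjusted differences EA–SEA, EA–SAC and SEA–SAC with confidence intervals. Use the same model for EASI and DLQI with their own baselines, where the assessment schedule (Figure 2, not visible in the text reviewed) provides them. Adding centre is optional, since randomisation is not stratified by it. If the analysis plan already specifies such a model, align the article's wording with it.

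The cost is analysis wording and one degree of freedom for the baseline term. For the primary outcome, no new patients, visits or measurements are needed.

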**Methods and analysis:**

This multicenter, single-blinded, randomized controlled trial is planned to transpire from April 15, 2023, to June 30, 2025. We will recruit 132 participants with AE (44 per group). Participants will be assigned randomly to three equal-sized groups: EA, sham electroacupuncture, and sham acupuncture. Treatment will be administered three times a week during the 2-week intervention phase. The primary outcome measure is the Visual Analog Scale, with a numeric rating scale to evaluate pruritus. Secondary outcome measures include the Eczema Area and Severity Index and Dermatology Life Quality Index. Other outcome measures include physical examination, serum IgE, and safety evaluation. The number, nature, and severity of adverse events will be carefully recorded.

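### The plan names the rank-sum test as its check for non-normality and the paired signed-rank test as an analysis for independent arms, so the rule for quantitative outcomes is incoherent as written

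*Protocol article*

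**What the plan says.** The Statistical analysis section gives quantitative data two routes. Normally distributed data go to a t-test, with a Satterthwaite correction for unequal variances, which is an unpaired comparison. For the rest: "Quantitative data exhibiting a non-normal distribution on the Wilcoxon rank-sum test will be analyzed using the Wilcoxon signed-rank sum test". The same sentence then adds covariance generalized linear models, without saying which of the two methods leads. No other normality check is named. Earlier in the same paragraph the rank-sum test appears as a comparative test, but for qualitative data.

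The arms are independent: "Participants will be assigned randomly to three equal-sized groups: EA, sham electroacupuncture, and sham acupuncture". Nothing in the article describes matching or crossover. The primary endpoint is quantitative: "The proposed study’s primary outcome is improved VAS scores after 2 weeks of treatment". It has no test of its own, so the general rule covers it by inclusion, not by name. The secondary outcomes EASI and DLQI fall under the same rule.

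**The concern.** Two tests are given jobs that they cannot do.

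- **The check.** A rank-sum p-value responds to a difference in location between two groups. Used to detect non-normality, it tends to flag data when the arms differ and to pass skewed data when they do not. The choice of analysis then depends on the treatment effect, not on the shape of the data.
- **The analysis.** The signed-rank test works on paired differences or a single sample. In a parallel three-arm trial it can be run only on arbitrary pairs of unrelated patients, or within one arm as a before–after test. Neither is a proper comparison of EA with a sham arm.

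What is at stake is whether the protocol fixes how the primary comparison will be made. A before–after result can be significant in every arm without any effect of EA, since the Basic treatment section gives all patients moisturiser and health guidance.

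**Working it through.** **1. The plan's own sample size.** The design inputs are "0.05, test efficacy 1-β = 0.8, two-sided test" and assumed means of "35.7% for the EA group, 40.4% for the sham electroacupuncture (SEA) group, and 45.9% for the sham acupuncture (SAC) group". The differences are EA–SEA 4.7, SEA–SAC 5.5 and EA–SAC 10.2. The stated results are "the sample content was calculated to be 35 cases per group and 105 cases for the three groups" and "Assuming a 20% dropout rate of patients at follow-up, we calculated the sample size to be 44 cases for each group".

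The dropout step reproduces: 35 / (1 − 0.20) = 43.75, rounded up to 44; 44 × 3 = 132. The 35 cannot be reproduced forwards, because the article gives no value for σ or τ. Solving its formula backwards, with k = z(1 − 0.05/(2τ)) + z(0.8):

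σ = Δ × √(35/2) / k, with k = 3.236, 3.083 and 2.802 for τ = 3, 2 and 1.

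**2. The rank-sum test as a normality check.** The planned EA–SEA difference in SD units is 4.7/σ. Each setting had 20,000 simulated trials of two normal arms with equal variance, n = 35 per arm. A trial counts as flagged when the two-sided rank-sum p < 0.05.

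| Difference that set n = 35 | τ | Implied σ | EA–SEA effect (SD) | Flagged "non-normal" |
|---|---|---|---|---|
| 4.7 | 3 | 6.08 | 0.77 | 87% |
| 4.7 | 1 | 7.02 | 0.67 | 77% |
| 5.5 | 3 | 7.11 | 0.66 | 76% |
| 5.5 | 1 | 8.21 | 0.57 | 63% |
| 10.2 | 3 | 13.19 | 0.36 | 30% |
| 10.2 | 1 | 15.23 | 0.31 | 24% |

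Allowing for rounding of n and simulation error, the range is about 24% to 88%. The formula's note, "representing the mean of any two groups, and n is the sample size of a pair of τ comparisons (taking the maximum value", points to the smallest difference and so to the upper rows, but it does not settle τ.

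Reverse case: two identical exponential arms, n = 35, are flagged in 4.9%. With identical lognormal arms at n = 44 the rank-sum test flags 4.7%, while a Shapiro–Wilk test flags 100%.

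**3. The signed-rank test across arms (n = 44 per arm).**
- Unequal arm sizes (44 and 42): the test cannot be computed.
- Equal sizes: the result depends on an arbitrary ordering. In one simulated data set, re-ordering one arm alone moved p over 0.18 to 0.83 (central 95%); the rank-sum test gives the single value 0.52.
- No true difference, arbitrary pairing: rejection in 5.4% (normal) and 5.2% (lognormal), so the size is kept.
- Lognormal arms shifted by 0.6 on the log scale (illustrative): power is 72.5%, against 78.0% for the rank-sum test.

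**4. The signed-rank test within an arm (n = 44).** The mean before–after changes below are illustrative; none is in the article. The SD is that of the change.

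| Mean change (SD) | p < 0.05 within the arm |
|---|---|
| 0.2 | 24% |
| 0.3 | 48% |
| 0.5 | 89% |

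These are rates of detecting a real change, and they carry no information about EA against sham. With the same true improvement of 0.42 SD in two arms, EA was significant and sham was not in 17.8% of runs.

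**The case against.** The strongest reply has four parts.

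- **The sentence does not end with the signed-rank test.** Covariance generalized linear models are named beside it and can compare arms validly. This stands. A reader might infer that the plan leaves non-normal data with no means of testing EA against sham, and the text does not support that. But the model is not made primary, and it too is reached through the rank-sum check.
- **It may be a slip of wording.** The authors may have meant a normality test first, then rank-sum between groups and signed-rank within groups. The unpaired t-test in the preceding sentence makes this plausible. The text does not say so, however. If signed-rank was meant only for before–after change, no non-parametric between-arm test is named for quantitative outcomes.
- **The article mentions a separate analysis plan, not shown here, which may set this out properly.** That limits any claim about what the analysts will actually do. It does not correct the published rule, which states something wrong and does not merely omit detail.
- **A reader might infer a raised false-positive rate.** The calculations do not show one: arbitrary pairing kept the size near 5%. Within-arm p-values would mislead only if reported as efficacy of EA, and the article does not say that they will be.

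**Conclusion.** Wrong as written. The stated rule for quantitative data, which takes in the primary VAS outcome, uses one test that does not measure normality and another that cannot compare independent arms. The plan therefore does not fix coherently how VAS, EASI and DLQI will be compared between arms.

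The structural conclusion needs no assumption beyond the text. The 24% to 88% range assumes normal data with equal variance, 35 per arm, a literal reading of the check, and a σ back-solved from the stated 35. The before–after rates rest on illustrative changes. The case does not extend to proven type I error inflation, nor to every method in the fallback being invalid.

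**What to change.** Amend the Statistical analysis section:

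1. Remove the rank-sum test as a check for non-normality.
2. State in advance one between-arm analysis for VAS, EASI and DLQI, for example the covariance model that the protocol already names.
3. Name the between-arm rank-sum test as the non-parametric alternative or robustness check.
4. Restrict the signed-rank test to before–after change within an arm, labelled descriptive.

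The cost is two sentences of analysis wording. The sample size stays at 44 per group and 132 in total.

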### Patients and public involvement

The patients and the public will not be involved in the design, conduct, reporting, or dissemination plans of our research.

## Discussion

AE and other allergies are becoming more common on globally (38). AE is a common, recurrent, and inflammatory skin condition. In China, 15–30% of dermatological outpatient cases have AE (39). One of the most common chronic conditions, AE, affects up to a fifth of the population in developed countries. It was once thought to be the initial symptom of atopy—the tendency for a family member to develop IgE sensitivity to environmental allergens—and the onset of “atopic march,” which ultimately leads to asthma and allergic rhinitis (40, 41). Quality of life and economic outcomes can be adversely affected, particularly for people with moderate to severe AE.

Itching is one of the most burdensome symptoms of AE; the problems caused by itching cannot be underestimated. Severe itching often leads to excessive scratching, which indirectly leads to lichenification, thus transitioning from acute to sub-acute eczema, and ultimately to relapsing AE. Therefore, one goal of AE treatment should be addressing the pruritic symptoms in patients.

AE has no curative therapy. The basic idea is to avoid certain triggers, continuously restore the epidermal barrier using emollients, and treat inflammation with TCSs or antihistamines. Because of the limited number of trials explicitly comparing medications, how well different treatments control the condition over time is unknown (42, 43).

Acupuncture, a complementary and alternative medicine approach, can help overcome these limitations, effectively relieve itching, and improve patients’ quality of life (44–46). EA decreases serum levels of neuropeptides and inflammatory factors, making it effective for allergic diseases, and has been increasingly utilized as an adjuvant therapy in routine eczema treatment. Numerous clinical studies on using acupuncture or EA for AE have been reported (47–52).

We propose a prospective, multicenter, randomized controlled study of AE. The multicenter model considers the effect of environmental factors and individual participant characteristics on trial results, providing more reliable clinical evidence. We designed three arms to compare the effectiveness of EA and acupuncture and to establish the genuineness and credibility of the acupoints while eliminating any potential placebo effect. The objective VAS score was adopted as the primary outcome measure, and the EASI and DLQI scores as the secondary outcome measures, which should improve the reliability of the results. In addition, physical examination, personal life history, safety evaluation, patient satisfaction, and other outcome measures have been added. Keeping participants closer to the clinic helps track the disease progression in a clinical setting.

The study design has limitations. First, the sample size is only 132 participants. Second, the study duration is limited to 3 weeks without a follow-up period. Observing the long-term effects of the EA anti-itch technique on the progression of AE with a limited sample size and follow-up period will be challenging. However, we will use unique experimental designs and outcome measures to improve the accuracy and sensitivity of this study to mitigate these limitations.

In summary, this multicenter, randomized, sham electroacupuncture–controlled study will assess the effect on pruritus, clinical efficacy, and safety of the acupuncture antipruritic technique in AE. We will also establish a multicenter clinical registration platform and evaluate clinical evidence by assessing the treatment’s therapeutic benefits (clinical effectiveness with no adverse side effects). The findings will aid decision-making for managing and treating AE and offer crucial data that could be integrated into future clinical recommendations.

